#### Recruitment

Consistent with our prior work, we took a multi-pronged approach to recruitment: posting flyers in targeted areas; performing outreach to agencies, clinics, community-based organizations, shelters, single room occupancy hotels; and accepting direct peer and provider referrals. Recruitment was conducted by experienced teams of transgender field staff. All interviews and intervention procedures were conducted at trans-friendly field sites where many transgender women live or congregate. In San Francisco, our field site was located in the Tenderloin area, and in Los Angeles our field site was located on the border between Hollywood and West Hollywood, areas with high HIV prevalence and community viral load burdens in San Francisco and Los Angeles. Both sites had working relationships with dozens of community-based agencies and clinics in the area. These connections, along with input from our community advisory boards and our strong working relationships with local agencies that serve transgender women, were used in recruitment efforts to meet project timelines. The enrolment period was conducted in 34 months. Recruitment efforts were monitored by study investigators. Individuals were paid $10 for completing eligibility activities and $30 for completing enrolment procedures. For complete incentive information, see Table 6. *Healthy Divas* incentive schedule.

**Table 6 T6:** *Healthy Divas* incentive schedule.

**Control**	***Healthy Divas*** **intervention**
$10 for completing the eligibility visit.	$10 for completing the eligibility visit.
$30 for completing all enrolment procedures.	$30 for completing all enrolment procedures.
$40 for completing 3, 6, 9, and 12 month follow up assessments.	$30 for completing each of the 6 individual sessions.
$10 for each check-in on months 2, 4, 5, 7, 8, 10, and 11.	$40 for attending the group workshop.
$40 for up to 4 successfully enrolled participants referred. $10 per enrolled referral.	$40 for completing 3, 6, 9, and 12 month follow up assessments.
	$10 for each check-in on months 2, 4, 5, 7, 8, 10, and 11.
	$40 for up to 4 successfully enrolled participants referred. $10 per enrolled referral.
Total possible: $310	Total possible: $530

#### Patient and Public Involvement

The development of the *Healthy Divas* intervention and the implementation of the RCT were informed by a Community Advisory Board comprised of transgender women living with HIV.

### Assignment of Interventions

#### Allocation

##### Sequence Generation

Participants were randomly assigned via stratified randomization with randomly permuted block sizes of 2, 4, and 6. There were eight strata based on site, age <40 years old vs. not, and binary race (Black vs. not for San Francisco and Latina vs. not for Los Angeles) with a 1:1 allocation to either *Healthy Divas* or control condition using a computerized secure and fraud-resistant procedure employed in our team's prior studies. Our experience with over 700 participants in three RCTs has indicated that this method is successful for achieving balance across demographic, mediating, and outcome variables.

##### Concealment Mechanism

Allocation concealment was ensured, as the randomization procedure did not release the randomization code (to participants or study staff) until the participant had been recruited into the RCT after all baseline measurements had been completed.

##### Implementation

The study statistician generated the randomization scheme using SAS v.9.3. The resulting allocation list was stored in the data collection software package, REDCap, and maintained by the statistician. The research team did not have access to the randomization scheme at any time. The next available randomization status from the appropriate strata for each individual participant was delivered to the research assistant at the time of randomization only by REDCap. The research assistants enrolled participants into their assigned study arms.

#### Masking

Masking was not used in this trial; therefore emergency unmasking was also not used in this trial. Outcome assessors were not masked in this RCT because they informed participants of their study condition assignment. Peer counsellors did not serve as outcome assessors.

### Data Collection, Management, Analysis

#### Data Collection Methods

Potential participants gave consent to be screened for eligibility. An eligibility survey was administered by study staff; confirmation that participants were living with HIV was achieved via evidence of one of the following: HIV ART medicine prescribed to the participant; other medical documentation; rapid HIV testing provided by study staff; having previously participated in another research study for people living with HIV at either study site; or contact with the participant's care provider through signing a release of medical information form. If found eligible and following consent to enroll in the study, participants had their blood drawn, completed the baseline survey, provided extensive locator information, and were randomized to either intervention or control group.

##### Primary Outcome

To determine whether TWH randomized to *Healthy Divas* will achieve or maintain higher rates of undetectable viral load than TWH assigned to a treatment as usual control condition, the primary outcome was assessed. This RCT's primary outcome was virologic control as indicated by an undetectable HIV-1 level (undetectability = < 20 copies/mL). Virologic control was conducted at baseline and at each follow-up assessment for 12 months post-randomization at 3-month intervals. A study phlebotomist performed peripheral venous blood sample collections. This process included: completing laboratory requisitions forms with collection date, time, and other relevant information; preparing two tubes for HIV-RNA; performing venipuncture and blood draw; spinning and freezing each specimen; placing each labelled specimen and requisition form in a shipment bag for pick up. Results were securely accessed through the Care360^TM^ platform in San Francisco and Foundation Laboratory in Los Angeles and entered and saved in a study password-protected Access form.

##### Secondary Outcomes

Secondary outcomes included a behavioral composite of engagement in HIV care scale (75), which integrates current/past ART use, HIV appointments timeline follow back, ART adherence (adherence rating (48) and visual analog scale (49)), and knowledge of current CD4 cell count, in addition to the intervention's hypothesized mechanisms of action. Surveys were administered at baseline and at each follow-up assessment for 12 months post-randomization at 3-month intervals using the audio computer-assisted self-interviewing (ACASI) system and REDCap. Data were collected and managed using REDCap electronic data capture tools at UCSF (79). REDCap (Research Electronic Data Capture) is a secure, web-based application designed to support data capture for research studies, providing: (1) an intuitive interface for validated data entry; (2) audit trails for tracking data manipulation and export procedures; (3) automated export procedures for seamless data downloads to common statistical packages; and (4) procedures for importing data from external sources. Research assistants set participants up to use the ACASI and REDCap systems for baseline and follow-up survey assessments. see Table 2 for a full list of the measures used, including scale names/sources, number of items, and Cronbach's alpha. Data quality was promoted through initial, follow-up, and ongoing training of staff members conducting assessments, in addition to regularly held quality assurance meetings.

#### Retention

Our retention plan, developed by our team, has successfully retained >90% of research cohorts per year, and we conservatively estimated 80% retention for the 12-month period (80, 81). The retention plan included: presence at a central location close to public transit; maintenance of detailed contact information; skilled staff trackers; a reliable monthly check-in program (see below); graduated incentive payments (see Table 6. *Healthy Divas* incentive schedule); and efforts to foster positive attachments to the study.

Each participant was scheduled for brief monthly check-in visits in months in which there was otherwise no scheduled visit. At this visit, which was highly flexible and could occur in person or by phone, we updated contact information, clarified the next study visit date and time, documented 30-day self-reported adherence and any changes in medication regimens, and recorded any provider visits that had occurred in the prior month. Participants were paid a small incentive for this 10-min visit ($10). For this study, each monthly check-in visit had the added benefit of documenting HIV care appointment attendance while the events were still recent, which improved precision of our self-reported retention in care measurement. This timeline follow-back procedure was used in our pilot with positive results. Staff members had previously reported information available to them to facilitate this data collection. For example, an interviewer was able to say, “The last time we spoke was on [date] and at that time you said you had seen Dr. [provider's name here] at [clinic or hospital name] on [date previously provided]. Since that visit with Dr. X, have you attended any appointments?” We also inquired about missed appointments (i.e., scheduled but not attended) during each time period.

#### Data Management

All data were password protected and backed up daily to an encrypted secure server. Electronic copies of the data were stored on a secure server and any paper copies were destroyed at the end of the study. Participants' identity and data were handled with highest levels of care and confidentiality. The exceptions to confidentiality were those defined by law and include a suspicion of child abuse, elder abuse, and threat of imminent action on suicidal or homicidal ideation. The information provided by participants is coded with a number to help protect privacy; the link listing names with numbers is kept in locked files. Only study staff had access to study files. Other entities who may access research data include UCSF Committee on Human Research; Western Institutional Review Board; National Institutes of Health (NIH); University of California; and Friends Research Institute. Reports and publications about the study will never refer to participants by name. All staff members were trained in procedures for maintaining confidentiality of participant information.

#### Statistical Methods

##### Analysis Population and Missing Data

For preliminary analyses and missing data, one-way frequency tables for all variables and measures of central tendency and variability for continuous variables will characterize the sample. These analyses will be stratified by randomization group (i.e., intervention vs. control) to check for imbalances. If the intervention and control groups are found to differ significantly at baseline on one or more covariates (e.g., on ART vs. not), we will use methods based on the Rubin causal model (e.g., propensity scores, targeted maximum likelihood estimation, double-robust estimation) to obtain the desired marginal effect estimates under the counterfactual assumption of balanced groups (82–86). In general, we will address incomplete data multiple imputation (MI) (87) because MI makes the relatively mild assumption that incomplete data arise from a conditionally random (MAR) mechanism rather than the completely random process (MCAR) assumed by *ad hoc* methods such as listwise data deletion (88). Auxiliary variables will be included in analyses involving incomplete data to help meet the MAR assumption (89, 90) and sensitivity analyses will be conducted with pattern-mixture models to assess the robustness of the MAR assumption (91). SAS (92) will be used to perform the proposed analyses.

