	Adherence self-efficacy	HIV-ASES (53)	12	0.74–0.90
	Treatment readiness	ART expectancies/readiness (54)	12	0.81–0.88
	Social support	Social support questionnaire (55)	6	0.94
	Coping	Coping self-efficacy scale (56)	13	0.80
	Patient communication	Patient communication index (57)	5	0.85
	Shared decision making	Autonomy preference index (58)Decision-making opportunity scale (59)Decisional balance (single item) (60)	6 3 1	0.82–0.84
**Background and potential moderators**	Background/demographic	Age, race, ethnicity, income, education, sex work, relationship status, housing stability, incarceration history, transgender-specific health care, CD4+ cell.	18	NA
	Experiences of transphobia	Experiences of transphobia (adapted from schedule of racist events) (61)	18	0.96
	Experiences of racism	schedule of racist events (61)	18	0.91
	History of trauma	Trauma history questionnaire (62)Recent trauma screening item (63)	24 1	0.85 NA
	Positive and negative affect	Depressive symptoms: CES-D scale (64)Positive / negative affect: differential Emotions scale (DES) (65, 66)	20 30	0.86–0.91
	HIV stigma	HIV Stigma Scale Sowell (67, 68)	12	0.86
	Substance use	DAST-10 (drug screening) (69)Alcohol use disorders identification test (AUDIT) (70)Drug use frequency (71, 72)	10 10 10	0.80–0.94
	Transgender identification	Adapted from multigroup ethnic identity measure (73)	13	0.82

Intervention delivery training included detailed review of the intervention approach, procedures, and research ethics. Population-specific training included how to address trans-specific issues and cultural issues specific to African American and Latina TWH. Specific techniques for adhering to a manualized intervention while allowing for flexibility to address individual participant needs were be taught, role-played and supplemented by instructional readings including one written by Co-I [name] (74). Ongoing training provided updates on HIV treatment and weekly group supervision; individual supervision addressed cases and procedural issues in intervention implementation. In this RCT, we offered the study in both English and Spanish.

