Therefore, we hypothesized that, following the intervention, the odds of undetectable viral load will be higher for intervention participants than for control participants (Hypothesis 1). Our primary interest was to estimate the marginal or population-average effect of intervention participation on each outcome rather than the effect for a hypothetical average subject. (93) Moreover, within-subject correlations among outcomes are considered nuisance parameters rather than quantities of interest to be modeled explicitly. Accordingly, generalized estimating equations (GEE) will be used to perform the proposed primary analysis, which is a planned time-averaged comparison of post-baseline measurements across the intervention and control groups to test primary Hypothesis 1. Alpha will be set at 0.05 for this planned comparison. Any additional *post-hoc* comparisons (e.g., paired comparisons of the control and intervention groups at each time point) will maintain a nominal alpha level of 0.05 through the use of simulation-based stepdown multiple comparison methods (94). Reflecting the binary nature of the virologic control outcome, a binomial distribution and logit link will be used for this analysis. Though GEE estimates are consistent even if the correlation structure is misspecified, GEE's statistical efficiency improves as the working correlation structure more closely approximates the actual correlation structure (95). Thus, working correlation structures suitable for the study's design will be considered (e.g., unstructured, AR (1), exchangeable, *M*-dependent) (96). The QIC statistic will be used to select the final working correlation structure (97). Robust Huber-White “sandwich” standard errors will be used to obtain correct inferences even if the chosen correlation structure remains slightly misspecified. GEE case deletion diagnostics (e.g., DFBetas, Cook's *D*) will be used to investigate whether influential cases are present; if such cases are found, results will be reported with and without influential cases included (98). As noted above, standard care quality (SCQ) will be included as a covariate in this analysis. In addition, randomization strata indicators will be included as covariates to obtain unbiased results (99). Additional covariates may be included if they improve QIC.

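### A baseline significance test and a QIC search can change the primary estimator, its covariates and the meaning of its odds ratio, and the protocol does not say which result is then primary

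*Protocol article*

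**What the plan says.** All places are in the protocol article.

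- **Statistical Methods, Analysis Population and Missing Data.** The baseline tables by arm serve to look for imbalance. "If the intervention and control groups are found to differ significantly at baseline on one or more covariates", with being on ART given as the example, then "we will use methods based on the Rubin causal model (e.g., propensity scores, targeted maximum likelihood estimation, double-robust estimation"). The stated purpose of the switch is "to obtain the desired marginal effect estimates under the counterfactual assumption of balanced groups". The three methods are examples, and none is chosen.
- **Statistical Methods, Outcomes.** "generalized estimating equations (GEE) will be used to perform the proposed primary analysis", a logit-link comparison averaged over the post-baseline visits at alpha 0.05. "standard care quality (SCQ) will be included as a covariate in this analysis", and indicators for the randomisation strata go in as well. The paragraph ends: "Additional covariates may be included if they improve QIC". Separately, "The QIC statistic will be used to select the final working correlation structure".
- **Table 2, background and potential moderators.** The variables open to a baseline comparison include "Age, race, ethnicity, income, education, sex work, relationship status, housing stability, incarceration history" and several psychosocial and substance-use scales. The background row alone counts 18 items.

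The article neither says which result is primary once the trigger has fired nor confines the causal-model methods to a sensitivity role.

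**The concern.** Allocation was 1:1, stratified and concealed. With sound randomisation, a significant baseline difference shows only that chance produced one. It does not show that the covariate predicts viral load, and prognosis is what decides whether adjustment helps. A rule built on that test therefore makes the analysis depend on a chance event unrelated to the need for adjustment.

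The second rule works on the outcome data, because QIC is computed from the fitted outcome model. The covariate set of the primary model is then known only after the outcome has been modelled.

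What is at stake is whether the primary result can be identified in advance. The trial is unmasked (Masking), all investigators hold the cleaned data (Access to Data), and analyses were starting at submission (Participant Timeline). If two or more permitted analyses disagree, the article gives no rule for choosing between them.

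**Working it through.** **1. The plan's own figures.** The article gives no figure for this point. Table 5 does show which quantity the trial was powered on. With 114 per arm, four visits and correlation ρ, the effective number per arm is 114 / [(1 + 3ρ)/4]. For P0 = 0.30 and ρ = 0.50 this is 114 / 0.625 = 182.4. The stated difference of 14.1 points gives an odds ratio of (0.441/0.559) / (0.30/0.70) = 1.84, as printed, and a two-sided 0.05 test of two proportions has power 0.799. So Table 5 is reproduced by a comparison of two proportions without covariates, that is, a marginal odds ratio.

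**2. How often the trigger fires by chance.** Assumptions: each test at 0.05 and k independent covariates; the article states neither. P(at least one significant) = 1 − 0.95^k.

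| k | 1 − 0.95^k |
|---|---|
| 5 | 22.6% |
| 10 | 40.1% |
| 18 | 60.3% |
| 25 | 72.3% |

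Correlated covariates give lower values. Site, age group and the race indicator are stratification factors and can hardly contribute.

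**3. Type I error.** A null simulation used 1,500 trials of 228 participants and 4 visits, with 18 independent covariates (4 of them prognostic) and an independence logistic GEE with sandwich standard errors. The trigger was represented by adjusting for the covariates found imbalanced. The Monte Carlo standard error at 5% is √(0.05 × 0.95 / 1,500) = 0.56 points.

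| Procedure | Rejection rate |
|---|---|
| One fixed model | 5.0% |
| Adjust for significant imbalances | 4.4% |
| Forward selection by QIC | 5.0% |
| Smallest p-value among the permitted models | 9.1% |

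The trigger fired in 60.7% of these trials, in line with step 2. A second simulation, with 278 participants, 20 candidate covariates (6 prognostic) and 2,550 replicates, gave 6.7% for QIC selection against 5.5% for a fixed set. Treated as independent proportions, the difference of 1.2 points has a standard error of √[(0.067 × 0.933 + 0.055 × 0.945) / 2,550] = 0.67 points, so z is about 1.8.

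**4. What the odds ratio means.** In a logit model, adding a prognostic covariate changes the quantity estimated even under perfect balance. Take a binary covariate split equally, with odds ratio 6 for the outcome and 50% control response overall.

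- Control odds in the two halves: 1/√6 = 0.408 and √6 = 2.449.
- A conditional odds ratio of 2.00 makes the treated odds 0.816 and 4.899, so the probabilities are 0.449 and 0.830, with mean 0.640.
- Marginal odds ratio: (0.640/0.360) / 1 = 1.78.

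With covariate odds ratios of 3 and 10, the same steps give 1.91 and 1.67. The covariate odds ratios are illustrative assumptions.

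**5. Which predictors are left to the data.** The statistical Outcomes section expects 20% of the sample to be off ART, and so detectable, and 40% to 60% to be detectable at baseline. It thus ties ART use and baseline virologic status to the outcome in advance. The fixed covariates are SCQ and the strata (site, age group, race). The two obvious predictors enter only through the trigger or the QIC clause.

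**The case against.** **The article condenses a fuller plan.** The test level, the candidate covariates and the exact estimator commonly sit in an analysis plan, which is not shown. This stands: their absence is no part of the point. The point rests on two rules that the article states affirmatively.

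**Several stronger readings are tempting, and the documents do not support them.**

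- A reader might infer that the trigger is almost certain to fire. Counting about 46 baseline items in Table 2 gives 1 − 0.95^46 = 91%. That requires counting every background item separately, adding measures that Table 2 lists as secondary outcomes and mediators, and assuming independence among plainly related scales.
- A reader might infer that the GEE is replaced. The text does not say so. The GEE is named as primary without condition, and propensity weights can be used inside a GEE. TMLE and double-robust estimation are different estimators, so what remains is an undefined relation between the two sections.
- A reader might infer that QIC selection makes the 5% test anti-conservative. One simulation shows no excess, and in the other the difference is about 1.8 standard errors. The 9.1% arises only if someone picks the smallest p-value, which the plan does not propose.

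**The plan's use of marginal can be defended.** The statistical Outcomes section contrasts a population-average effect with one for a hypothetical average subject, which is the usual case for GEE over a random-effects model. The planned GEE already conditions on SCQ and the strata. That is fair, but the trigger sentence uses the same word for a counterfactual average over covariates. The two routes can therefore report different quantities under one name.

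**Much is already fixed:** alpha, SCQ, the strata and robust standard errors. QIC selection of the working correlation is minor given the sandwich errors. This limits the severity.

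**Conclusion.** The point holds, as a should-fix. A chance baseline result can call in a different class of estimator, and an outcome-based criterion can change the covariates of the primary model. The article does not say which result then counts. The trigger fires by chance in roughly 23% to 72% of trials for 5 to 25 independent covariates tested at 0.05. Those inputs are assumptions, and correlation would lower the figures.

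Inflated type I error under mechanical use is not shown. The exposure is discretionary choice among permitted analyses (9.1% at worst in one simulation, under its assumptions) and an odds ratio whose meaning shifts: a conditional 2.00 corresponds to a marginal 1.67 to 1.91 for the covariate strengths tried. The plan also leaves to chance or to model fit the two covariates that its own reasoning marks as prognostic.

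**What to change.** 1. Delete the significance trigger and the clause admitting covariates by QIC. Keep QIC for the working correlation only.
2. Name the GEE as the primary analysis, with a closed covariate set used whatever the observed balance: randomisation strata, SCQ as already planned, baseline virologic status and ART use at baseline.
3. State the target. Either standardise the fitted model over these covariates and report the marginal effect, or say plainly that the odds ratio is conditional on them.
4. Keep one named propensity-score, TMLE or double-robust analysis, with the same covariates, as a sensitivity analysis.
5. Date the change and disclose how much of the data had been seen, because analyses were starting and the investigators had access to the cleaned data.

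With a fixed estimator and covariate list, the chance that baseline tests alter the primary analysis falls to zero. The cost is analysis-plan wording, a standardisation step and a disclosure. The analyst gives up the freedom to add covariates after seeing the data.
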